## Abstract

**Background:**

Many therapeutic interventions are performed by physiotherapists to improve upper extremity function and/or activities of daily living (ADL) in stroke patients. Mirror therapy (MT) is a simple technique that can be self-administered by the patients with intact cognition following patient education by a skilled physiotherapist. However, the effectiveness of self-administered MT in post-stroke patients in upper extremity function remains unclear. Therefore, the objective of this study is to examine the effectiveness of MT in improving upper extremity function and recovery in acute stroke patients.

**Methods:**

This study is a single-center, prospective, randomized, open-label, controlled trial with blinded outcome evaluation (PROBE design), in which a total of 36 eligible acute stroke patients will be randomly assigned to control (n=18) and experimental group (n=18). Participants in the control group will receive regular rehabilitation interventions whereas participants in the experimental group will receive MT education in addition to their regular interventions for 4 weeks.

**Study outcome:**

The primary outcome measure will be upper extremity function that will be measured using the Fugl-Meyer Assessment scale and the Wolf Motor Function Test. The secondary outcome measure will be behaviors related to ADL as estimated using the Modified Barthel Index. Outcome measures will be assessed at baseline and at 4 weeks post-rehabilitation intervention/MT.

**Results:**

A two-way repeated analysis of variance (ANOVA) with time and group effects will be used to analyze between-group differences. The level of significance will be set at *P* < 0.05.

**Conclusion:**

The results of the study will provide critical information to include self-administered MT as an adjuvant to regular interventions and may facilitate recovery of the upper extremity function of stroke patients.

**Trial registration:**

ClinicalTrials.gov NCT04542772. Registered on 9 September 2020. Protocol version: Final 1.0.

## Background

Stroke is a sudden loss of brain function caused by focal cerebral ischemia or hemorrhage resulting in neurological impairments [1]. According to available statistics from 2012 to 2013, the number of stroke survivors in Canada is equivalent to the population of New Brunswick. It is the third leading cause of death and physical disability in Canadian adults [2]. Unfortunately, up to 78% of stroke survivors have impaired upper extremity function resulting in diminished activities of daily living [3]. Evidence shows that stroke survivors with initial upper extremity weakness can regain function using therapeutic interventions [4]. The Canadian Stroke Best Practice Guidelines (CSBPG) outlined specific therapies, such as range-of-motion exercises, mental imagery, functional electrical stimulation, mirror therapy (MT), constraint-induced movement therapy, virtual reality, strength training, and bilateral arm training, to improve upper extremity function [5]. While the majority of these therapeutic procedures are administered by skilled professionals, mirror therapy is a simple and inexpensive technique that can be self-administered by the patients with intact cognition.

In MT, the patient is seated with a lap tray and a mirror is placed in between the arms in midsagittal plane with the mirror facing the unaffected arm. The patient is asked to move the unaffected arm while looking at the mirror. The patient perceives the reflection in the mirror as his paralyzed arm and the brain receives a stimulus as if the patient is moving his affected arm. This visual stimulus supports motor rehabilitation by capitalizing on the strong connection between visual input and the premotor cortex [5, 6]. The effectiveness of MT in upper extremity function has been well explored in the past [7–11].

## Critical review

In an effort to identify gaps in the literature and to identify the parameters that can be used for our study, published systematic reviews and meta-analyses on the use of mirror therapy on upper extremity function in post-stroke patients were reviewed. A total of 49 studies were identified in six systematic reviews [12–17]. We categorized those 49 studies as acute/early sub-acute stroke (< 4 weeks), sub-acute stroke (< 3 months), and chronic stroke (> 3 months) based on the initiation of intervention from stroke onset [7]. Of these 49 studies, five studies (Table 1) were conducted on acute/early sub-acute stroke patients and were included for critical analysis (Table 2) [8–11, 18]. We found that the included five studies had limited sample sizes, weak methodology, and MT intervention were therapist guided. The frequency and duration of the MT intervention ranged from 5 days/week, 30 min/session for 2 weeks to 5 days/week, and 30 min/session for 6 weeks. The type of exercise training varied across all 5 trials. Bilateral arm training was included in one study [7], unilateral movement in two studies [8, 11], MT combined with constraint-induced movement therapy in one study [10], and MT combined with neuro-muscular electrical stimulation in one study [9]. In all five studies, it was concluded that MT was effective in improving the upper extremity function of stroke patients.

**Table 1 Tab1:**
[figure not shown]
Primary studies included in systematic reviews

**Table 2 Tab2:** Sample size, risk of bias, and PEDro scores

Reference	Sample size and dropouts	Cochrane risk of bias tool				PEDro score	Who led MT intervention?
		Random allocation (selection bias)	Allocation concealment (selection bias)	Incomplete outcome data (attrition bias)	Blinding of outcome assessment (detection bias)		Therapist/ Patient
Dohle et al., 2009 [8]	48 and 12	Low	Low	High	Low	7/11	Therapist
Invernizzi et al., 2013 [9]	26 and 1	Low	Low	High	Low	6/11	Therapist
Yun et al., 2011 [10]	60 and not reported	Low	High	High	High	5/11	Therapist
Yoon et al., 2014 [11]	26 and not reported	Low	High	High	High	5/11	Therapist
Cristina et al., 2015 [16]	15 and not reported	Low	High	High	Low	5/11	Therapist

Reported: low risk, not reported: high risk

The effectiveness of MT was summarized in one of the recent Cochrane reviews which included randomized controlled trials (RCTs) and randomized cross-over trials comparing MT and other interventions. The results suggested moderate-quality evidence that MT has a significant effect on motor function with SMD 0.47, 95% CI 0.27–0.67 for all outcome measures and mean difference of 4.32, 95% CI 2.46–6.19 for Fugl-Meyer Assessment upper extremity [19]. The authors suggested that MT should be considered, at least, as an adjuvant to conventional rehabilitation to improve upper extremity motor impairments and ADL of stroke survivors [17].

Morkisch et al. performed a secondary meta-analysis on a Cochrane review for MT to detect which parameters of the therapeutic protocols influence the effect of MT in upper extremity rehabilitation in post-stroke individuals. They found that unilateral arm movement execution without manipulation of objects with a larger mirror was found to be more effective in improving motor function than bilateral movement including manipulation of objects with using a smaller mirror [12]. The use of a larger mirror (50 x 40 cm) lessens the distraction and increases unilateral visual feedback. In addition, the larger mirror allows incorporation of shoulder movements and shaping (adaptation of the content of the therapy) [18]. Evidence shows that mirrored movements of the unaffected limb resulted in sufficient neural activation, without movement of the paretic limb [20, 21].

Patient self-managed education program has been shown to be effective in improving patient outcomes and in reducing treatment costs in other clinical conditions [22]. In addition, there is evidence that self-delivered MT intervention is feasible and improves patient outcomes in other clinical conditions [23]. Although the effect of patient education and effectiveness of MT are extensively explored in separate studies, the effectiveness of self-administered MT has not been explored in acute stroke patients. Also, literature shows that rehabilitation interventions are crucial during the first 4 weeks post-stroke as it is a critical time for neural plasticity and recovery [7]. Therefore, the objective of the present study is to examine the effectiveness of MT in improving upper extremity function and recovery in acute care settings.

## Material and methods

### Study design

A single-center, prospective, randomized, open-label, controlled trial with blinded outcome evaluation (PROBE design) will be used to evaluate the effectiveness of self-administered MT on upper extremity functions of acute/or early sub-acute stroke patients.

### Study setting

The study will be conducted at the acute stroke and intensive rehabilitation units at one of the Ontario hospitals between July 2021 and June 2022. We assessed feasibility of single-center study by reviewing The Discharge Abstract Database (DAD) which revealed approximately 300 stroke annual stroke admissions for the last two fiscal years. This will allow sufficient patient recruitment (calculated below) over 1 year period for the study.

### Study participants

A stroke team member at the hospital will identify potential patients, and a physiotherapist will assess patient eligibility based on the following inclusion: (1) > 18 years of age; (2) any gender; (3) admitted with a diagnosis of stroke with onset within 2 weeks; (4) Brunnstrom stages of stroke recovery between 2 and 4 for the upper extremity; (5) able to follow directions; (6) no severe cognitive impairments that could interfere with patient participation; (7) consent to treatment by the patient; and (8) Alpha-Functional Independence Measure (Alpha-FIM) score of > 40. Patients will be excluded based on several criteria: (1) medically unstable patients; (2) lack of motivation; (3) recurrent/chronic stroke; (4) recent upper extremity musculoskeletal injuries with movement restrictions; (5) receptive or global aphasia; (6) delirium; (7) unilateral neglect; and (8) visual field defect.

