### Outcome measures and data collection

The primary outcome measures of interest are the level of upper limb motor impairment and functional performance. These variables will be measured using the Fugl-Meyer Assessment-upper extremity (FMA-UE) and the Wolf Motor Function Test (WMFT), respectively. Both FMA-UE and WMFT are reliable and valid outcome measures and are used consistently in MT research [25]. Moreover, the Stroke Edge Task Force of the Academy of Neurological Physical Therapy (American Physical Therapy Association) recommends FMA-UE and WMFT for patients who have had a stroke and who are undergoing acute care [26]. The secondary outcome measure will be ADL measured by the Modified Barthel Index (MBI), a reliable and valid tool for assessing ADL in stroke survivors and used in MT research.

A physiotherapist will assess the above outcome measures twice: (1) pre-test assessment at the beginning of the trial and (2) post-test assessment at the end of the trial. Before the study, the assessor will be trained in assessing all outcome measures and will be tested with two patients to assure standardization. The assessors will be trained by one of the investigators of this study (VR) who is a physiotherapist specialized in stroke rehabilitation and experienced in administering the above outcome measures. In addition, demographic characteristics, such as age, gender, handedness, Alpha-FIM score, Brunnstrom stages of motor recovery, type of lesion, side of hemiplegia, and the onset of stroke, will be collected during the initial assessments (Fig. 2).

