### Participant timeline

Participant timeline was developed according to the SPIRIT guideline and is presented in Table 3.

**Table 3 Tab3:** Timeline of screening, recruitment, randomization, interventions, and assessments

Time point	Study period		
	0 week (w)	4 w	Closeout (4 w)
Enrollment			
Eligibility screen	x		
Informed consent	x		
Allocation	x		
Intervention			
Experimental group	x	x	
Control group	x	x	
Assessments			
Demographics	x		
FMA-UE	x	x	
WMFT	x	x	
MBI	x	x	

*FAM-UE* Fugl-Meyer Assessment-upper extremity, *WMFT* Wolf Motor Function Test, *MBI* Modified Barthel Index

Rehabilitation interventions are crucial during the first 4 weeks post-stroke as it is a critical time for neural plasticity and recovery [17]. Therefore, the present study will be initiated within 48 to 72 h of patient admission in the acute care unit and will be continued for 4 weeks following the initial assessment. Following admission to an acute stroke unit, screening and informed consent and baseline outcome assessments will be completed within 48 to 72 h. The mirror therapy education will commence immediately after the baseline assessment and end in 4 weeks.

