### Statistical analysis

#### Data analysis

Data will be analyzed using the SPSS software version 23. Demographic characteristics and baseline scores will be compared using the independent *t*-test and the chi-squared test for continuous variables (such as age and time since stroke) and dichotomous variables (gender, dominance, affected side, and type of lesion), respectively. A two-way repeated analysis of variance (ANOVA) with time and group effects will be used to analyze between-group differences. We will administer both intention-to-treat and per-protocol analyses to determine the effectiveness of the proposed intervention [27]. The level of significance will be set at *P* < 0.05. Patients will be considered as being compliant if they perform at least 80% of the original MT protocol. The compliance will be reported using the four ways recommended by Hawley-Hague et al. (i.e., completion, attendance, duration adherence, and intensity adherence) [28]. In addition, CONSORT will be used to report this RCT to facilitate reading and quality assessment.

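### Treatment may start anywhere from about day 2 to day 17 after the stroke; days since onset is recorded, but the stated outcome model leaves it out

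*Protocol article*

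**What the plan says.** Four statements in the protocol article bear on this point.

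- **Eligibility (Study participants).** Patients must be "admitted with a diagnosis of stroke with onset within 2 weeks". The cap on entry is therefore counted from stroke onset.
- **Start and length of treatment (Participant timeline).** The study "will be initiated within 48 to 72 h of patient admission in the acute care unit", and "The mirror therapy education will commence immediately after the baseline assessment and end in 4 weeks". Treatment start is counted from admission. The reason given just before is that "Rehabilitation interventions are crucial during the first 4 weeks post-stroke as it is a critical time for neural plasticity and recovery".
- **Data collected (Outcome measures and data collection).** Among the demographic items, "side of hemiplegia, and the onset of stroke, will be collected during the initial assessments".
- **Analysis (Data analysis).** Baseline comparability is to be checked with independent t-tests for "continuous variables (such as age and time since stroke" and chi-squared tests for dichotomous variables. The outcome comparison is a repeated-measures ANOVA with two factors, time and group. No covariate is named, and no consequence is attached to the result of a baseline test.

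**The concern.** The protocol bases its timing on the idea that recovery potential depends on how recent the stroke is. If so, the change expected over four weeks without mirror therapy differs between a patient who starts on day 2 and one who starts on day 17. With two assessments per patient, the group-by-time test compares four-week changes between arms. Subtracting each patient's own baseline score need not remove a difference in expected change.

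Two things are at stake. With 18 patients per arm, the arms may differ by chance in mean days since onset, and that difference passes into the estimated effect. The spread in days since onset also stays in the residual variance, although the variable that could remove part of it is already recorded.

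The one stated use of the variable helps with neither. Under valid randomisation, a baseline significance test examines a null hypothesis that is true by design. It flags only the extreme imbalances and corrects none of them.

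**Working it through.** The plan gives no figure of its own on this point, so the check builds on its timing rules.

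**1. Start and end of treatment, in days from onset.** Inputs: onset to admission 0 to 14 days (Study participants); admission to start 2 to 3 days (Participant timeline); course of 28 days.

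- Earliest: start 0 + 2 = day 2, end 2 + 28 = day 30.
- Latest: start 14 + 3 = day 17, end 17 + 28 = day 45.
- Treatment days within the first 28 after onset: 28 − 2 = 26 (93%) for the earliest starter and 28 − 17 = 11 (39%) for the latest.
- If the two-week limit applies at enrolment instead of at admission, the latest start is about day 14, which leaves 14 of 28 days (50%).

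**2. Chance imbalance between arms of 18.** The documents do not give the distribution of start days, so these are assumptions. SE of the difference in means = SD × √(2/18) = SD/3; 95% range = ±1.96 × SE.

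- Uniform on days 2 to 17: SD = 15/√12 = 4.33; SE = 1.44; range ±2.8 days.
- Uniform on days 2 to 14: SD = 12/√12 = 3.46; SE = 1.15; range ±2.3 days.
- Starts clustered early, SD 2 days: SE = 0.67; range ±1.3 days.

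**3. What the baseline t-test does.** At 18 per arm the two-sided 5% critical difference is 0.677 SD, or 0.677 × 4.33 = 2.9 days under the first assumption. That this lies next to the 95% chance range is true by construction and is no discovery. It does mean that, in about 19 of 20 properly randomised trials, whatever imbalance occurred would be reported as non-significant. In the remaining one the plan states no action.

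**4. Size on the outcome scale, illustration only.** Assume natural recovery with gain = R × exp(−t/τ) × (1 − exp(−28/τ)), R = 20 recoverable FMA-UE points, and τ of 21 or 42 days. None of these comes from the documents.

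- τ = 21: 13.4 points from day 2 against 6.6 from day 17. The difference of 6.8 over 15 days is about 0.46 points per day.
- τ = 42: 9.3 against 6.5. The difference of 2.8 over 15 days is about 0.19 points per day.
- Times ±2.8 days: 0.5 to 1.3 points, or 12% to 30% of the mean difference of 4.32 quoted in the Critical review section.
- Times ±1.3 days: about 0.2 to 0.6 points.

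**5. Precision.** Adjusting for a covariate with correlation ρ to the outcome cuts residual variance by ρ². At 18 per arm, 80% power and two-sided 5%, the detectable standardised difference without adjustment is 0.96.

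- Assumed ρ of 0.3 to 0.5: variance falls by 9% to 25%, and the detectable difference to 0.92 to 0.83.
- Using step 4 instead: the quoted 4.32 and SMD of 0.47 suggest an SD near 4.32/0.47 = 9.2 (rough, since the SMD covers all motor outcomes). The covariate then contributes an SD of 0.19 × 4.33 = 0.8 to 0.46 × 4.33 = 2.0 points, or about 1% to 5% of the variance.

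The plausible gain in precision thus runs from negligible to useful, and the documents do not settle where it lies.

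**The case against.** Much of the opposing case stands.

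- **The comparison is randomised.** The control arm recovers over the same calendar of entry, so spontaneous recovery does not compete with mirror therapy as an explanation of a between-arm difference. Chance imbalance is already allowed for in the standard error, and the unadjusted test keeps its type I error. A reader might infer that the result would be confounded; the documents do not support that. What adjustment offers is an estimate corrected for the imbalance that actually occurred, and some precision.
- **The article is condensed.** Covariates are commonly named in the full protocol or analysis plan, and their absence alone would not be worth raising. Here, however, the article states the outcome model and assigns this very variable to a baseline test. The comment is on that stated choice.
- **The size is assumed.** The recovery curve, the recoverable points and the start-day distribution are not in the documents. Early clustering is plausible for an acute stroke unit and halves the imbalance.
- **Other covariates could be chosen.** Brunnstrom stage and Alpha-FIM are also recorded, and nothing shows that days since onset predicts best. It is, however, the one variable that the protocol itself links to recovery potential.

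Three further readings are tempting and should be resisted. Entry is timed from onset, through the two-week cap; only treatment start follows admission. The protocol does not claim that the course lies within the first four weeks: it says that period matters, and its Critical review section classes studies by when the intervention begins, which every patient here meets. Nor does the article say that allocation is simple; it describes a software-generated sequence with 18 per arm and does not give the method.

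**Conclusion.** The point holds as a modest, practical weakness of the stated analysis. By the protocol's own rules, treatment may start from about day 2 to day 17 after onset (about day 14 at most on the narrower reading of the limit). The recorded time since onset goes only into a baseline test that neither reliably detects nor corrects imbalance at 18 per arm.

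The cost is uncorrected chance imbalance of up to about ±2.8 days if start days are uniform on 2 to 17, and less if starts cluster early, together with lost precision that may be anywhere from about 1% to 25% of residual variance under the assumptions shown. No firm figure in FMA-UE points can be given. The point shows no systematic bias and no invalid test, and it is no argument for changing who is enrolled or when treatment begins.

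**What to change.** In the Data analysis section, pre-specify days from stroke onset to baseline as a covariate in the FMA-UE, WMFT and MBI group comparisons, to be used whatever the baseline t-test shows. Its form matters:

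- In the repeated-measures ANOVA it must enter with its interaction with time. A main effect alone leaves the group-by-time contrast unchanged.
- Alternatively, use an ANCOVA of the four-week score on group, baseline score and days since onset.

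The Group assignment section places randomisation before the baseline assessment. Counting the days to allocation instead would make the covariate strictly pre-randomisation; given the 48 to 72 hour window, this moves it by three days at most.

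The cost is a sentence of text and one degree of freedom per model. No new data are needed, because onset is already collected and must be known to apply the eligibility criterion. The Trial status section reports that nobody had been recruited, so by that statement pre-specification was still possible. Stratifying the allocation on time since onset is optional: the documents offer no basis for a cut-point, and in 36 patients a stratum could be sparse.

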### Group assignment

#### Sample size estimates

The sample size and effect size were calculated based on a previously published study [24], using the G* power software. A sample of 18 will be required in each group to detect a difference in the primary outcome measure (FMA-UE) with an effect size (Cohen’s d) of 1.15 and a statistical power of 0.80 at a one-sided type one error of 0.05.

Based on the above calculation, a total of 36 patients will be recruited and assigned to the MT (n = 18) or control group (n =18) using a random sampling method. Randomization will be done prior to the baseline assessment with a statistical software program that generates this sequence. Random numbers will be assigned according to the order of patients’ admission to the hospital. To *conceal allocation*, random group allotment will be managed by a social worker who will not be involved in the assessment or intervention to minimize the confounding and contamination. Refer to Fig. 1 for the study process.

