### Limitations

A limitation of this study is having two primary outcome measures which affects the power of the study. However, we decided to include both the outcome measures as we are interested in exploring the effectiveness of MT in improving motor impairment and motor function.

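### The sample size of 18 per group does not follow from its stated inputs (they give 11), and its one-sided alpha does not match the planned ANOVA F test

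*Protocol article*

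**What the plan says.** Under Sample size estimates, the protocol article gives the group size and the outcome it is meant for: "A sample of 18 will be required in each group to detect a difference in the primary outcome measure (FMA-UE". The standardised effect assumed there is 1.15. The power and error rate attached to this number are "a statistical power of 0.80 at a one-sided type one error of 0.05". As to their source, the article reports that they "were calculated based on a previously published study [24], using the G* power software". The recruitment target of 36, split 18 and 18, is then drawn directly from that calculation. The section gives no inflation for dropout, for two primary outcomes or for anything else.

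Under Data analysis, the test is named: "A two-way repeated analysis of variance (ANOVA) with time and group effects will be used to analyze between-group differences". The threshold there is a P value below 0.05, as it is in the abstract. Neither place mentions a one-sided test. Under Limitations, the authors acknowledge the cost of two primaries: "A limitation of this study is having two primary outcome measures which affects the power of the study".

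**The concern.** The article gives everything a two-group calculation needs: a standardised effect, power, alpha, sidedness, equal allocation and the software. A reader can therefore repeat it, and an effect as large as d = 1.15 should need far fewer than 18 per group at 80% power.

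The second difficulty is that the size is justified one-sided, while the analysis rests on an ANOVA F test. An F test rejects for a difference in either direction. With two groups and two time points, the group-by-time F test is the same as a two-sided t test on change scores. The stated power therefore describes a test that the analysis section does not plan.

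At stake is how the result will be read. Power and detectable effect tell a reader what a null or positive finding from 36 patients means. As printed, these figures cannot be reproduced, and the error rate differs between two sections.

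**Working it through.** **Inputs (protocol article, Sample size estimates):** d = 1.15; power 0.80; one-sided alpha 0.05; 1:1 allocation; stated answer n = 18 per group. Because d is standardised, no SD is needed.

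**Method:** two independent means, noncentral t (G*Power's method for this design). With n per group, df = 2n − 2 and noncentrality δ = d·√(n/2). One-sided power is P(T > t₀.₉₅,df), where T is noncentral t with parameter δ. For a two-sided test, replace t₀.₉₅ by t₀.₉₇₅; the opposite tail is negligible here.

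**Step 1: try to reproduce 18.**

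| n per group | Test | df | δ | Critical t | Power at d = 1.15 |
|---|---|---|---|---|---|
| 10 | one-sided 0.05 | 18 | 2.571 | 1.734 | 0.796 |
| 11 | one-sided 0.05 | 20 | 2.697 | 1.725 | 0.831 |
| 12 | two-sided 0.05 | 22 | 2.817 | 2.074 | 0.768 |
| 13 | two-sided 0.05 | 24 | 2.932 | 2.064 | 0.803 |

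The stated inputs give 11 per group (22 in total). A two-sided test gives 13 (26 in total). The article's 18 (36 in total) is not reproduced. The normal approximation agrees: 2(1.645 + 0.842)²/1.15² = 12.37/1.3225 = 9.35, so 10 per group before the small-sample correction.

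**Step 2: what 18 per group delivers.** Here δ = 1.15·√9 = 3.45 and df = 34.

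- One-sided 0.05 (critical t 1.691): power 0.959.
- Two-sided 0.05 (critical t 2.032): power 0.918.
- d detectable with 80% power: 0.85 one-sided, 0.96 two-sided.

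**Step 3: can a standard variant explain 18?**

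| Variant (d = 1.15 unless noted) | n per group |
|---|---|
| Mann-Whitney, one-sided 0.05, 80% power | 12 to 13 |
| Mann-Whitney, two-sided 0.05, 80% power | 14 to 16 |
| Two-sided 0.025 (assumed split over two primaries), 80% power | 16 |
| One-sided 0.05, **95%** power | 18 |
| **d = 0.85**, one-sided 0.05, 80% power | 18 |
| Two-sided 0.05, 80% power, plus an assumed **25% loss** (13/0.75 = 17.3) | 18 |
| d taken as a post-test difference, change scores analysed, assumed pre-post correlation **0.3**, two-sided 0.05 | 18 (one-sided: 14) |

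Exactly 18 appears only when a stated input is changed or an unstated one is added. From the one-sided 11, dropout would have to be 1 − 11/18 = 39%. Several routes lead to 18, and the article does not say which was taken.

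**Step 4: sidedness.** A two-group F test with f = d/2 = 0.575 at 0.05 needs 26 in total and has power 0.918 with 36. These equal the two-sided t results, which confirms that the planned test corresponds to the two-sided column.

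**The case against.** The strongest reply is that the error is on the safe side. The trial will recruit 36, and the stated inputs need only 22 one-sided or 26 two-sided. Correcting the paragraph changes no patient, test or threshold. That stands, and it sets the severity: this is a fault of reproducibility and consistency, not a trial too small for its stated effect.

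Three stronger readings are tempting, and the document does not support them.

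- *A reader might infer that one-sided 0.05 leaves room to claim success at a two-sided P below 0.10.* The abstract and the Data analysis section both fix the ANOVA at P < 0.05, and one-sided appears only in the sample size sentence. Such a claim would contradict the analysis section as written.
- *A reader might infer that the missing attrition allowance endangers the trial, since Table 2 lists 12 dropouts of 48 in one earlier study.* At the stated d, 18 per group can fall to 13, a loss of 5/18 = 28%, and still hold 80% power two-sided. No practical harm follows at that d.
- *A reader might infer that 18 was built as 13 plus dropout.* Nothing in the article says so, and 95% power or d = 0.85 explains 18 equally well. Table 2 gives dropouts for only two of its five studies.

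The objection does not rescue the calculation itself. The article is a condensed account, but these figures are stated, not left to another document, and they disagree.

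**Conclusion.** The point holds, with moderate severity. For d = 1.15, 80% power and one-sided 0.05, the required size is 11 per group, not 18. The overstatement is 7 per group, or 14 in total. At 18 per group, the power for that d is 96% one-sided or 92% two-sided, not 80%. At least one of power, d and n is wrong, or an allowance is unstated. Separately, the one-sided alpha conflicts with the non-directional F test at P < 0.05.

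The 92% figure depends on three conditions:

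- **d = 1.15 must be the correct input.** If the misprinted figure is d, the 92% falls with it.
- **d must refer to the contrast tested**, such as the difference in change for the group-by-time term. If d is a post-test difference and the group main effect is tested, power at 18 per group is about 0.55 to 0.42 for assumed pre-post correlations of 0.3 to 0.8 with equal baselines.
- **There must be no loss and no alpha split.** With an assumed two-sided 0.025 for each of the two primaries, 80% power needs 16 per group, power at 18 is 0.86 and power at 13 is 0.70.

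The detectable d of 0.96 (two-sided, 80% power) does not depend on the cited effect, but it too assumes 18 evaluable per group and no split.

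**What to change.** Keep 36 patients. Then:

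1. Retrieve the original G*Power output, find which figure (power, d or n) was misreported or which allowance was left out, and correct it in the sample size section.
2. State two-sided 0.05 in both the sample size and Data analysis sections.
3. Name the FMA-UE contrast to which d refers, and say what 18 per group delivers for it: 80% power for d = 0.96, two-sided. Quote 92% power only if d = 1.15 is confirmed and refers to that contrast, and say that it is before any loss or any alpha split for the two primary outcomes.
4. Do not present 28% attrition as the original rationale. Mention a dropout margin only if the retrieved calculation contained one, or label it as a consequence of the restated figures.

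The cost is one rewritten paragraph and one added phrase, with no change in enrolment. The Trial status section reports no patients recruited at its stated date, so a correction made at that stage would precede any data.
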